**27. APPENDIX G: AMENDMENT HISTORY**

| Amendment No. | Protocol Version No. | Date issued | Author(s) of changes | Details of Changes made                                                                                                                                                                                                                          |
|----------------------|-----------------------------|--------------------|-----------------------------|---------------------------------------------------------------------------------------------------------------------------------------------------------------------------------------------------------------------------------------------------------|
| 1.0                  | 2.0                         | 05/01/2023         | [name]       | 1. Update of section 11.11 to allow for health economic evaluation                                                                                                                                                                                      |
| 2.0                  | 3.0                         | 27/02/2023         | [name]       | 2. Removal of bars and mouses as the new supplier of meal replacement products does not provide them. However, the new products adhere the same legislation and are interchangeable nutritionally to the original supplier.
3. Correction of a typo. |
| 3.0                  | 4.0                         | 12/09/2023         | [name]       | 1. Revisions to exclusion criteria on dietary requirements, insulin use, and risk of intestinal obstruction.
2. Update of administrative details.                                                                                                    |
| 4.0                  | 5.0                         | 07/06/2024         | [name]             | 1. Update of study synopsis with extension to planned recruitment period.                                                                                                                                                                               |
| 5.0                  | 6.0                         | 19/06/2024         | [name]             | 1. Correction of typo to protocol version/date number.                                                                                                                                                                                                  |

|  |  |  |  |                                           |
|--|--|--|--|-------------------------------------------|
|  |  |  |  | 2. Formatting
numbering
correction. |
|--|--|--|--|-------------------------------------------|

List details of all protocol amendments here whenever a new version of the protocol is produced.

Protocol amendments must be submitted to the Sponsor for approval prior to submission to the REC committee and HRA (where required).

[figure not shown]

## 1. INTRODUCTION

This document details the proposed data presentation and analysis for the main paper(s) and final study reports from the National Institute for Health Research-funded study named “Pre-operative intentional weight loss to support post-operative recovery in patients with overweight and colorectal cancer: the CARE feasibility randomised controlled trial”. The results reported in these papers should follow the strategy set out here. Subsequent analyses of a more exploratory nature will not be bound by this strategy, though they are expected to follow the broad principles laid down here. The principles are not intended to curtail exploratory analysis (for example, to decide cut-points for categorisation of continuous variables), nor to prohibit accepted practices (for example, data transformation prior to analysis), but they are intended to establish the rules that will be followed, as closely as possible, when analysing and reporting the trial. This document follows published guidelines regarding the content of statistical analysis plans for clinical trial (Gamble et al).

The analysis strategy will be available on request when the principal papers are submitted for publication in a journal. Suggestions for subsequent analyses by journal editors or referees, will be considered carefully, and carried out as far as possible in line with the principles of this analysis strategy. If reported, the analyses will be marked as post-hoc and the source of the suggestion will be acknowledged.

Any deviations from the statistical analysis plan will be described and justified in the final report of the trial. The analysis should be carried out by an identified, appropriately qualified and experienced statistician or researcher, who should ensure the integrity of the data during their processing. Examples of such procedures include quality control and evaluation procedures.

Integral to this Statistical Analysis Plan (SAP) is the SAP – Data Definitions and Tables document which will include full detailed descriptions of all key outcomes, including their definition, generation and how they will be reported at the end of the study. These two documents should be read in tandem.

## 1.2 Changes from previous version of SAP

This is a summary of key changes from earlier versions of SAP, with particular relevance to protocol changes that have an impact on the design, definition, sample size, data quality/collection and analysis of the outcomes will be provided. The protocol version number and date are included.

| Version number
Issue date | Author of this
issue | Protocol Version & Issue
date | Significant changes from previous
version together with reasons                                                                                                                                                                                                                                |
|------------------------------|-------------------------|----------------------------------|---------------------------------------------------------------------------------------------------------------------------------------------------------------------------------------------------------------------------------------------------------------------------------------------------|
| V0.1_08Dec2022               | [name]             | CARE protocol v1.0 181122        | Not applicable as this is the 1 st issue                                                                                                                                                                                                                                               |
| v0.02_06Feb2023              | [name]   | CARE protocol v1.0 181122        | First draft                                                                                                                                                                                                                                                                                       |
| v0.03_21Feb2023              | MH & DK                 | CARE protocol v1.0 181122        | Second draft                                                                                                                                                                                                                                                                                      |
| V1.0_14Mar2023               | MH & DK                 | CARE protocol v3.0 270223        | Clean version 1.0                                                                                                                                                                                                                                                                                 |
| V2.0_07Oct2024               | MH & DK                 | CARE protocol v6.0 190724        | Clean version 2.0. Changes since 1.0 are: 
 
Recruitment period end changed from June 2024 to November 2024
 
"Definition of Analysis Populations" expanded to include patients who had their surgery less than 20 days since randomisation
 
 |
|                              |                         |                                  | Add to or delete as required                                                                                                                                                                                                                                                               |

## 2. BACKGROUND AND OBJECTIVES

### 2.1 Brief synopsis

This trial is a study of a pre-operative intentional weight loss intervention intended to support post-operative recovery in patients with overweight and colorectal cancer, aka “the CARE feasibility parallel randomised controlled trial”. It is intended to examine the feasibility of progression to a definitive randomised controlled trial that will examine whether a supported weight loss intervention aimed at overweight adults awaiting colorectal cancer surgery can reduce complications.

## 3. STUDY METHODS

### 3.1 Trial Design/framework

*See also the protocol section “Study Design”, “Synopsis”, “Description of the Statistical Methods”*

This is a prospective randomised controlled trial (RCT) with two arms, one for the intervention, one for the control. The timing is as follows

- Total trial length: 5.5 years
- Recruitment period: approx. 21 months (planned for March 2023 to June 2024, later November 2024)
- Individual participant’s involvement: approx. 2-3 months
- Long-term follow-up via medical records: up to 3 years

The trial will have an embedded evaluation and optimisation of the recruitment process (QuinteT). Participants will be recruited from hospitals across England.

Participants are expected to be involved in the study for approximately 2-3 months. They will be asked to attend hospital visits for screening, pre-operatively (on the day of surgery), and 30 days post-operatively. They will also remotely complete questionnaires at 1-3 days pre-operatively and have a semi-structured qualitative interview over the phone. The intervention will be delivered over the pre-operative period.

The study flow-chart can be seen in the appendices. At the end of follow-up the outcomes will be summarised and presented.

### 3.2 Randomisation and Blinding

*See also the protocol section “Randomisation” and “Blinding and code-breaking”*

Participants will be randomised by the local research team intended to conduct randomisation through a minimisation module on REDCap.

There are two arms, one for the intervention, one for the control.

Eligible participants will be individually randomised with a 1:1 allocation ratio to receive either the intervention or the control through minimisation with a 20% random element. The two stratified variables will be performance status (“0” vs “1-2”) and age at diagnosis (“< 70 years” and “≥70 years”) with the threshold of 70 chosen as the median age of diagnosis of colorectal cancer.

Allocation concealment is achieved as randomisation occurs after the baseline visit, the randomisation algorithm is unmodifiable and concealed from investigators and the local research teams, and the local research teams have no access to the total number of participants randomised to each group.

It is impossible to blind the participants and research nurses due to the nature of the intervention. Therefore, procedures for breaking the allocation code are not applicable. However, the assessors of the future primary outcome (research nurses conducting the post-operative follow-up visit) will be blinded. The central study team (chief investigator and members of the trial management committee) will be blinded to the adverse events and all post-operative data by trial group. The trial statistician is not blinded.

Full details of the randomisation are available in the latest RBP (Randomisation and Blinding Plan), which is stored in the confidential statistical section of the TMF.

### 3.3 Sample Size, hypothesis testing, and progression decision

*See also the protocol section "Sample Size Determination"*

With 72 patients (n=36 per arm), the trial will be 90% powered at one-sided 5% level based on the normal approximation approach to detect whether the proportions for the engagement, adherence, and retention criteria in the table 1 are truly above the upper limit of the red zone (>50% engagement, >35% adherence, >65% follow-up) based on an alternative being in the green zone. The collective power for the three criteria of engagement, adherence, and retention is 85% ( $93\% \times 92\% \times 99\%$ ) at 5% level to detect "GO" signals, without multiple testing adjustment. Recalculating the sample size on a binomial approach (sensitivity analysis) provided almost identical estimates.

We are testing against the upper limit of the red zone when the lower limit of the green zone is hypothesised to be true, therefore:

- Null hypothesis: True feasibility outcome is not greater than the upper limit of the red zone.
- Alternative hypothesis: True feasibility outcome is greater than the upper limit of the red zone.

### 3.4 Statistical Interim Analysis, Data Review and Stopping guidelines

*See also the protocol sections "Decision Points", "Stopping Rules" and "Study Committees"*

#### 3.4.1 Interim Analysis

No interim analysis is planned.

#### 3.4.2 Stopping rules

The TSC may formally recommend early termination if needed in line with the TSC charter.

#### 3.4.3 Trial Steering, Data Monitoring, and Ethics Committee (TSDMEC)

As this is an unblinded trial (with blinded outcome assessment), a separate Data Monitoring and Ethics Committee (DMEC) is not required. The independent Trial Steering Committee (TSC) will instead assume the role of the Data Monitoring and Ethics Committee. The resultant TSDMEC will comprise of an independent Chair (academic colorectal surgeon), two independent academics, independent statistician, and a patient and public representative.

### 3.5 Timing of Final Analysis

*See also the protocol section “Decision Points”*

The final analysis will occur at the end of the trial and no interim analysis is planned.

### 3.6 Blinded analysis

*See also the protocol section “Blinding And Code-Breaking”*

The nature of the study precludes the majority of blinding, however the central study team (chief investigator and members of the trial management committee) will be blinded to the adverse events and all post-operative data by trial group. The study statistician, who will not be blinded to these data, will prepare relevant reports of these data that will be reviewed in the closed sessions of the Trial Steering, Data Monitoring, and Ethics Committee.

### 3.7 Statistical Analysis Outline

*The statistical analysis of the study’s three primary outcomes and other outcomes is detailed in the protocol section “Statistics And Analysis”, a summary of which is given below:*

The study is a feasibility study intended to derive data, not to conduct formal statistical tests on them. Consequently, the outcomes will be summarised and described, not subjected to tests.

Table(s) will present the baseline demographic and clinical characteristics. Continuous variables will be summarised using means, standard deviations, and 95% confidence intervals. Medians with interquartile ranges will be presented where appropriate. Categorical variables will be summarised using counts and percentages. Exploratory between-group comparisons will be reported where appropriate. Any specific statistical analysis of the data will be carried out using appropriate statistical software. Any other analysis done by the Trial Statistician will be done by that software deemed sufficient by the Trial Statistician.

The data fall into two broad categories: the *primary outcomes* (referred to as “trial progression criteria”) and the *secondary and other outcomes*. They are treated as follows:

#### 3.7.1 Primary outcomes (referred to as “trial progression criteria”)

The trial progression criteria will be summarised descriptively for all participants [and by trial group, trial site, and neoadjuvant treatment (yes/no) as appropriate]. Uncertainty in the progression criteria will be expressed with 95% confidence intervals as well with two-sided 90% confidence intervals (given the one-sided 5% level in the sample size calculation). This uncertainty will be descriptive and will not be considered in the decision to progress to the definitive trial.

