### 11.3. Sample Size Determination

With 72 patients (n=36 per arm), the trial will be 90% powered at one-sided 5% level based on the normal approximation approach to detect whether the proportions for the engagement, adherence, and retention criteria in Table 2 are truly above the upper limit of the red zone (>50% engagement, >35% adherence, >65% follow-up) based on an alternative being in the green zone.[70] The collective power for all three criteria is 85% at 5% level, without multiple testing adjustment. Recalculating the sample size on a binomial approach (sensitivity analysis) provided almost identical estimates.[70]

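### The 5% level and 85% collective power in SAP 3.3 and protocol 11.3 belong to a test that plays no part in the progression decision

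*Combined protocol and SAP*

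**What the plan says.** SAP 3.3, whose heading covers sample size, hypothesis testing and the progression decision together, states: "With 72 patients (n=36 per arm), the trial will be 90% powered at one-sided 5% level based on the normal approximation approach". The null is set out as: "Null hypothesis: True feasibility outcome is not greater than the upper limit of the red zone". The alternative is the lower limit of the green zone. The collective power of 85% is given as the product of 93%, 92% and 99%, and is said to apply "at 5% level to detect 'GO' signals, without multiple testing adjustment". GO is not defined. Protocol 11.3 repeats the claim: "The collective power for all three criteria is 85% at 5% level, without multiple testing adjustment".

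SAP 3.7 then says: "Consequently, the outcomes will be summarised and described, not subjected to tests". SAP 3.7.1 provides 90% intervals because of the one-sided 5% level used for sample size, and adds: "This uncertainty will be descriptive and will not be considered in the decision to progress to the definitive trial". After SAP Table 1, each of criteria 2 to 4 takes a red, amber or green signal from its zone. Once recruitment and safety are at least amber, the worst of those signals decides.

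**The concern.** Whether a definitive trial is justified is the trial's only primary objective, so the error rates of that decision matter. A steering committee or funder reading SAP 3.3 or protocol 11.3 will naturally take 5% and 85% as the chances of a wrong and a right signal. The test carrying those figures is never performed, and its interval equivalent is excluded from the decision. Once uncertainty is set aside, only the observed percentage remains to place a criterion in a zone. That rule has its own error rates, and neither document states them.

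**Working it through.** **Inputs.** Red limits are 50%, 35% and 65%, and lower green limits 75%, 60% and 85%, for engagement, adherence and retention (SAP Table 1). Denominators are 36, 36 and 72. The 72 for retention is inferred: 36 would give 88% power, not the stated 99%. Criteria are taken as independent, as the SAP's own product implies. Engagement is treated as binary. SAP Table 3 defines it as a mean percentage per participant, so its figures are approximate.

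**Step 1: reproduce the 85%.** One-sided 5%, arcsine normal approximation: power = Φ(2[asin√p1 − asin√p0]√n − 1.645).

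- Engagement: 0.5236 × 6 − 1.645 = 1.497, giving 93.3%.
- Adherence: 0.5061 × 6 − 1.645 = 1.391, giving 91.8%.
- Retention: 0.4707 × 8.485 − 1.645 = 2.349, giving 99.1%.
- Product: 84.8%, matching 93% × 92% × 99% = 84.7%.

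Exact binomial tests reject at 24/36, 18/36 and 54/72, with levels of 3.3%, 4.6% and 4.6%. Their power is 90.8%, 91.7% and 99.1%, product 82.6%. The plan's arithmetic stands.

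**Step 2: the rule as written.** The chance of a signal is P(X ≥ r), with X binomial(n, p) and r the smallest count in the zone.

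| Criterion | Not RED from | GREEN from | Not RED, truth at red limit | GREEN, truth at red limit | GREEN, truth at green limit |
|---|---|---|---|---|---|
| Engagement | 19/36 | 27/36 | 43.4% | 0.2% | 58.8% |
| Adherence | 13/36 | 22/36 | 50.7% | 0.1% | 51.8% |
| Retention | 47/72 | 62/72 | 53.4% | <0.01% | 47.6% |

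If 47/72 (65.3%) counts as red, the 53.4% becomes 43.6%.

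**Step 3: overall signal at the green limits.**

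- Overall GREEN: 0.588 × 0.518 × 0.476 = 14.5%. If 61/72 (84.7%) is rounded to 85%, retention becomes 60.5% and the product 18.5%.
- Overall not RED: 0.9989 × 0.9989 × 1.0000 = 99.8%.

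The 85% fits neither reading of GO.

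**Step 4: one criterion at its red limit, the others at their green limits.** Overall not RED is 43% (engagement), 51% (adherence) or 53% (retention).

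**Step 5: away from the red limit.**

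| True value | P(not RED) |
|---|---|
| Adherence 20% | 2% |
| Adherence 25% | 9% |
| Adherence 30% | 26% |
| Adherence 45% | 89% |
| Retention 55% | 5% |
| Retention 60% | 21% |
| Retention 70% | 84% |

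**Step 6: where test and rule part.** Counts of 13–17/36 for adherence and 47–53/72 for retention are AMBER, although the exact one-sided 5% test would not reject the red-limit null. For example, 13/36 is 36%, with an exact 90% interval of 23% to 51%.

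**The case against.** The strongest reply is that the plan discloses its choice. SAP 3.7.1 says openly that uncertainty is left out, SAP 4.1 and protocol 11.7 call the intervals nominal, and SAP 3.7.1 itself ties the 5% level to the sample size calculation. Sizing on a test and then reading a traffic light is a coherent feasibility design. That stands, and it is why the rule itself need not change. It does not rescue the SAP's attachment of the 85% to GO signals.

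A reader might infer that any truly red criterion slips through about half the time. The documents do not support that: any cut-off on an observed value is passed about half the time when the truth sits on it, and the chance falls quickly below the limit (Step 5). Nor does either document state that a red criterion escapes only 5% of the time. They give a level for a test, not a misclassification rate for the zones. The slippage is also to AMBER, which means progressing with changes; recruitment and safety gate the decision as well.

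It is also fair that the stated alternative is exceeding the red limit, not reaching green. On that reading 99.8% is the relevant figure and is better than 85%. The 14.5% applies only if GO means overall GREEN, and it multiplies three probabilities near one half. The SAP leaves that meaning open. Finally, exact engagement figures would need a standard deviation that the documents do not give. A roughly symmetric mean would still clear a cut-off equal to its true value about half the time.

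**Conclusion.** The point holds as a mismatch between stated figures and the applied rule. The 5%, 90% and 85% describe a test outside the decision. The rule's own figures are about 14.5% overall GREEN (18.5% with rounding) and 99.8% overall not RED at the green limits, and 43–53% AMBER or better for a criterion at its red limit.

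These rest on independence, full denominators of 36, 36 and 72, and binary engagement. The adherence and retention rows do not depend on the engagement assumption; the overall figures do.

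Two stronger inferences should be resisted. The sample size is not miscalculated. Nor do the documents require the interval to decide RED.

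**What to change.** Keep the zones and the point-estimate rule.

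- In SAP 3.3 and protocol 11.3, label the 5% level, 90% power and 85% collective power as the sample-size rationale for a test that does not drive the decision.
- In SAP 3.3, delete the reference to GO signals, or define GO as overall GREEN or overall not RED.
- State the rule's operating characteristics at the red limits, at the green limits, and at values between and below them. Give the rounding convention at zone edges and note that engagement is approximate.

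The cost is wording in two documents, with the protocol change going through its amendment route. No data, threshold or analysis changes. The downside is that the stated figures look less favourable.

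Letting the lower 90% limit decide RED is an optional design choice, not a required fix. With exact limits it would need 18/36 for adherence and 54/72 for retention, overriding part of the published amber zones. True adherence of 45% would then be RED 67% of the time against 11% now, and true retention of 70% would be RED 79% against 16%. It would also need a named interval method: Wald limits would admit 53/72, at a level of 7.7%.
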